## Abstract

**Background:**

Haemorrhoids (piles) are a very common condition seen in surgical clinics. After exclusion of more sinister causes of haemorrhoidal symptoms (rectal bleeding, perianal irritation and prolapse), the best option for treatment depends upon persistence and severity of the symptoms. Minor symptoms often respond to conservative treatment such as dietary fibre and reassurance. For more severe symptoms treatment such as rubber band ligation may be therapeutic and is a very commonly performed procedure in the surgical outpatient setting. Surgery is usually reserved for those who have more severe symptoms, as well as those who do not respond to non-operative therapy; surgical techniques include haemorrhoidectomy and haemorrhoidopexy. More recently, haemorrhoidal artery ligation has been introduced as a minimally invasive, non destructive surgical option.

There are substantial data in the literature concerning efficacy and safety of 'rubber band ligation including multiple comparisons with other interventions, though there are no studies comparing it to haemorrhoidal artery ligation. A recent overview has been carried out by the National Institute for Health and Clinical Excellence which concludes that current evidence shows haemorrhoidal artery ligation to be a safe alternative to haemorrhoidectomy and haemorrhoidopexy though it also highlights the lack of good quality data as evidence for the advantages of the technique.

**Methods/design:**

The aim of this study is to establish the clinical effectiveness and cost effectiveness of haemorrhoidal artery ligation compared with conventional rubber band ligation in the treatment of people with symptomatic second or third degree (Grade II or Grade III) haemorrhoids.

Design: A multi-centre, parallel group randomised controlled trial.

Outcomes: The primary outcome is patient-reported symptom recurrence twelve months following the intervention. Secondary outcome measures relate to symptoms, complications, health resource use, health related quality of life and cost effectiveness following the intervention.

Participants: 350 patients with grade II or grade III haemorrhoids will be recruited in surgical departments in up to 14 NHS hospitals.

Randomisation: A multi-centre, parallel group randomised controlled trial. Block randomisation by centre will be used, with 175 participants randomised to each group.

**Discussion:**

The results of the research will help inform future practice for the treatment of grade II and III haemorrhoids.

**Trial Registration:**

ISRCTN41394716

## Background

Haemorrhoidal tissue, which forms the ‘anal cushions’, is a normal component of the anal canal and is composed predominantly of vascular tissue, supported by smooth muscle and connective tissue. Haemorrhoids result from enlargement of the haemorrhoidal plexus and pathological changes in the anal cushions. They are common, affecting as many as 1 in 3 of the population
[1]. Approximately 23,000 haemorrhoidal operations were carried out in England in 2004/5
[2] and the prevalence may be even higher in professionally active people. Repeated visits to hospital for therapy represent a significant disruption to the personal and working lives for this population in particular.

Treatment is dictated by the degree of symptoms and the degree of prolapse, and ranges from dietary advice to rubber band ligation (RBL) in the outpatient department, to an operation under general or regional anaesthetic. Although RBL is cheap, it has a high recurrence rate and patients often require further visits to the outpatient department for repeat banding before exploring surgical options
[3]. Although there are some variations (such as ligasure haemorrhoidectomy), surgery is commonly traditional "open" haemorrhoidectomy (OH) or a stapled haemorrhoidopexy (SH); both require an anaesthetic. OH is associated with considerable post-operative discomfort, sometimes necessitating overnight hospital stay and a delay in return to normal activity, but has a low recurrence rate; SH has a slightly higher recurrence rate but is carried out as a day case and patients return to normal activity more quickly
[4]. An alternative treatment is haemorrhoidal artery ligation (HAL), which also requires an anaesthetic, but is thought to enable even quicker return to normal activity. Recurrence rates are reportedly similar to SH but complication rates are lower
[5].

There are substantial data in the literature concerning efficacy and safety of RBL including multiple comparisons with other interventions
[6-12]. Recurrence varies from 11% to over 50%. This broad range probably reflects the definition of recurrence (patient symptoms or clinical appearance), the grade of haemorrhoids treated (grade I know prolapse; grade II spontaneously reducible prolapse; grade III prolapse requiring manual reduction; and grade IV un-reducible prolapse), the number of treatments and/or the intensity and length of follow up. In most studies, the incidence of recurrence is more than 30% and appears greatest for grade III haemorrhoids. Pain is common for a few hours following RBL and occasionally patients experience pain so severe as to require admission to hospital (around 1%
[3]), bleeding (3-4%, sometimes necessitating further treatment
[10]) and vaso-vagal symptoms (3%
[13]). There have also been rare incidences of blood transfusion
[14,15] and severe pelvic sepsis with a few instances leading death
[13]. Recurrences can be treated by re-banding or by surgical intervention.

Although HAL requires an anaesthetic, evidence suggests a recovery similar to RBL but an effectiveness that approaches the more intensive surgical options. The substantial data concerning effectiveness includes one recent systematic review
[5], three Randomised Control Trials (RCTs)
[16-18], one non-randomised trial
[19] and over 20 case series. A recent overview has been carried out by the National Institute for Health and Clinical Excellence (NICE), which concludes that current evidence shows it to be a safe alternative to OH or SH
[20], this is summarised below.

In terms of efficacy, studies with more than 1 year follow up suggest bleeding, pain on defecation and prolapse (surrogates of recurrent symptoms) in 10%, 9% and 11% of patients respectively

Regarding safety, post-operative haemorrhage requiring intervention (readmission, transfusion, reoperation or correction of coagulopathy) was reported in less than 1.2%, haemorrhoidal thrombosis was seen in less than 3.5% and fissure formation in less than 2.1%

The data from the three RCTs comparing HAL with SH and OH is difficult to combine, but efficacy seems similar for all procedures, with OH perhaps being superior in treating prolapse, although it is unclear if a "pexy" stitch was used in the HAL cases to reduce prolapse. OH appears to lead to the most post-operative pain and longest recovery. There are conflicting results as to whether the HAL technique results in less pain compared with SH. Complications were also more frequent in the OH group but occurred at a similar frequency when SH and HAL were employed.

Both the systematic review and the NICE overview highlight the lack of good quality data as evidence for the advantages of the technique; most data is from case series. Even the RCTs have significant methodological drawbacks that make them subject to selection, performance, attrition and detection bias. Indeed none of the studies are powered to reach any meaningful conclusion. There are no existing studies that compare HAL with RBL.

## Methods/design

The trial will be co-ordinated from the Clinical Trials Research Unit (CTRU) in Sheffield School of Health and Related Research (ScHARR). Delegated study staff located at individual centres will identify and consent potential participants. Potential participants will fall into three groups:

1. Patients presenting to the surgical outpatient clinic (SOPC) with symptomatic haemorrhoids that do not require further tests. This group will be identified by the clinical team from the GP referral letter and a patient information sheet sent to them prior to their clinic appointment. If they are willing to participate they will be consented and randomised when they attend the appointment.

2. Patients presenting to the SOPC with symptomatic haemorrhoids that require further tests to exclude other diagnoses. This group will be identified by the clinician at the clinic appointment and given a patient information sheet. They will undergo the necessary outpatient tests (usually endoscopy) and if negative (i.e. the symptoms are due to haemorrhoids) they will be contacted by the research nurse prior to attending their follow-up clinic appointment. They will then be randomised and consented when they re-attend the clinic.

3. Patients who return to SOPC following one unsuccessful RBL. They will be identified by the clinician at their first clinic appointment (when they have RBL) and given a patient information sheet. They will be contacted prior to a follow-up appointment (usually six weeks after treatment) by a research nurse. If they remain symptomatic and are willing to participate, they will be consented and randomised when they re-attend.

Thus, in each group, there is opportunity to provide the patient information sheet prior to a clinic appointment. Patients with investigations excluding pathologies other than haemorrhoids, and all those who have undergone rubber band ligation, will be contacted by the research nurse before the planned follow up clinic to ascertain whether they meet entry criteria and are interested in entering the trial. They will then be seen by the consultant and research nurse in clinic where recruitment and randomisation will take place.

After consent, participants will be individually randomised to HAL or RBL in equal proportion at all centres using a remote, web-based randomisation system.

Data will be collected to establish which patients have further treatment for recurrent symptoms or complications following their initial procedure. This will be achieved at the six week clinic visit following the intervention and by interrogating hospital records, asking the patients’ consultants, writing to patients’ GPs and questioning the patient via telephone interview at 12 months. Due to appointment availability the six week clinic visit may actually vary from four to twelve weeks following the intervention; this window is seen as clinically relevant.

### Participants

The target population will be patients referred to collaborating centres for treatment of haemorrhoids. 350 participants will be recruited from surgical departments in up to 14 NHs hospitals. Adults aged 18 years or over with symptomatic second or third degree haemorrhoids, either presenting for the first time or after one failure of RBL will be eligible to take part in the research.

### Exclusion criteria

Patients with certain pre-existing medical conditions will be excluded: patients with known perianal sepsis, inflammatory bowel disease, colorectal malignancy, pre-existing sphincter injury, or an immunodeficiency. Pregnant women and patients that are unable to have general or spinal anaesthetic are excluded as well as patients currently taking certain medication: Warfarin, Clopidogrel and Nicorandil.

Patients that are unable to give full informed consent (this may be due to mental capacity or language barriers) and patients previously randomised to this trial will be excluded from taking part in the research.

### Proposed sample size

Assuming the proportion of patients who experience recurrence following RBL is 30% and following HAL is 15%, the sample size required to detect a difference in recurrence rates with 80% power and 5% significance is 121 individuals per group. In order to account for any between-surgeon variation and loss to follow-up, we propose increasing this to 175 per group. This increase is based on the conservative assumption that there will be 14 surgeons in the trial (one per centre) and intra-class correlation (ICC) of 2.5% in keeping with typical ICCs observed by Ukoumunne
[21]. A more likely scenario is that each site will have a minimum of two surgeons, in which case the power to detect this difference is 85%; if there is no between-surgeon variation, the power will be 90%. Because the surgical procedure is well-developed and standardised, intra-class correlation should be virtually zero and the proposed sample size should have closer to 90% power.

The impact of loss to follow up will be minimal for the primary endpoint (haemorrhoidal recurrence at 12 months). Patients who do not complete their 12-month follow-up will have their hospital notes reviewed and their GP will be written to in order to ascertain whether any complications or operative procedures were recorded. The only drop-out expected would be where the patient dies, moves out of the area, or has no traceable patient notes, and we anticipate this would be less than the 5% we have now allowed for in this patient population (a previous study of RBL which used only clinical follow up, reported a 1-year loss to follow up of 10%
[22]).

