### Outcomes

The primary outcome measure is ‘recurrence’, defined as the proportion of patients with recurrent haemorrhoids at 12 months, as derived from a telephone assessment in combination with GP and hospital records.

The trial is a pragmatic design with a dichotomous outcome. As no validated symptom score exists, we have based our definition of recurrence on Shanmugam et al.’s systematic review
[6] definition:

1. Cured or improved: Symptom free or mild residual symptoms but not requiring further treatment at the end of study period; or,

2. Unchanged or worse: No symptom improvement and requiring further intervention or suffered complication or deterioration of symptoms.”

This study will simplify Shanmugam's criteria into the following question, asked at 12 months by a research nurse:

‘At the moment, do you feel your symptoms from your haemorrhoids are:

1. Cured or improved compared with before starting treatment; or,

2. Unchanged or worse compared with before starting treatment?’

Any patient who answers ‘1’ but has required further treatment since the initial procedure will be reclassified as ‘2’, identified via hospital records, their consultant, their GP and patient questioning.

Secondary outcome measures:

1. Symptom score (adapted from Nystrom et al.
[23])

2. Health related quality of life (using the EuroQol-5D “The EuroQoL group”
[24])

3. Continence questionnaire (using the validated Vaizey Incontinence Score
[25])

4. Pain score (using a 10 cm visual analogue scale)

5. Surgical complications

6. Need for further treatment including details

7. Clinical appearance of haemorrhoids at proctoscopy following recurrence

8. Health care costs

9. Cost effectiveness

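### Patients with no 12-month answer but traceable notes are counted as followed up for the primary outcome, although records cannot supply the patient's own rating

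*Protocol article*

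**What the plan says.** Under Outcomes, the primary outcome is recurrence at 12 months, "as derived from a telephone assessment in combination with GP and hospital records". A research nurse asks whether symptoms are cured or improved, or unchanged or worse, compared with before treatment. Records then work in one direction only: a patient who gives the favourable answer but has needed further treatment is moved to the unfavourable category. The abstract likewise calls the outcome patient-reported.

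Under Proposed sample size, patients who do not complete 12-month follow-up have their hospital notes reviewed and their GP written to, in order to "ascertain whether any complications or operative procedures were recorded". The section then states that "The only drop-out expected would be where the patient dies, moves out of the area, or has no traceable patient notes", expects this to be below the 5% allowed for, and opens the paragraph with "The impact of loss to follow up will be minimal for the primary endpoint". For contrast it cites an earlier banding study that relied on clinical follow-up alone and lost 10% at one year.

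**The concern.** The two sections treat a missing telephone answer differently. Under Outcomes, the answer is the starting point and records can only worsen the classification. Under Proposed sample size, a patient with no answer but traceable notes is not a drop-out, so that patient must carry a primary outcome. If the notes show further treatment, the outcome is recurrence. If they show nothing, no information on symptoms exists, and the only category left is non-recurrence.

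Patients with persisting symptoms who were not re-treated would then be scored as successes, and the missing rating would appear as observed data. Recurrence would be understated in both arms. If non-response differs by arm, the treatment comparison would be biased too.

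The search for these patients is also worded more narrowly than the endpoint. It names complications and operative procedures, while Outcomes and the data-collection paragraph in Methods/design refer to further treatment. The Background says recurrence can be treated by re-banding. A recorded complication is not in itself a route to recurrence under the trial's simplified question.

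**Working it through.** **1. The plan's own figure.** Inputs from Proposed sample size: 30% with RBL, 15% with HAL, 5% significance (taken as two-sided), 80% power. With the pooled-variance formula and no continuity correction:

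n = [1.96 × √(2 × 0.225 × 0.775) + 0.8416 × √(0.30 × 0.70 + 0.15 × 0.85)]² / 0.15² = (1.1575 + 0.4889)² / 0.0225 = 120.5, so 121 per group.

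This matches the stated 121. At 175 per group without clustering, the same method gives 92.3% power, or 90.9% after 5% loss (166.25 per group), against the stated 90%. The sample-size arithmetic is sound.

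**2. Effect of counting clean notes as non-recurrence.** Let m be the share with no 12-month answer and s the share of their recurrences visible in records. If non-responders have the same true recurrence rate as responders:

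observed rate = true rate × [1 − m(1 − s)]

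The values m = 5% and m = 10% are the document's own loss figures. All other values of m, and all values of s, are assumptions.

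**3. Equal non-response in both arms**, s from 0 to 0.75, 175 per group, no clustering:

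| m | RBL rate | HAL rate | Difference (points) | Power |
|---|---|---|---|---|
| 5% | 28.5–29.6% | 14.3–14.8% | 14.3–14.8 | 90.5–91.9% |
| 10% | 27.0–29.3% | 13.5–14.6% | 13.5–14.6 | 88.5–91.4% |
| 20% | 24.0–28.5% | 12.0–14.3% | 12.0–14.3 | 83.5–90.5% |

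Example: m = 10%, s = 0 gives 0.30 × 0.90 = 27.0% and 0.15 × 0.90 = 13.5%. If all non-responders were simply removed, power would be 90.9%, 89.4% and 85.6%. Little power is lost either way.

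**4. Unequal non-response**, s = 0.5. The true difference is 15 points and the true odds ratio (HAL to RBL) is (0.15/0.85)/(0.30/0.70) = 0.41:

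| Non-response RBL / HAL | RBL rate | HAL rate | Difference (points) | Odds ratio |
|---|---|---|---|---|
| 20% / 10% | 27.0% | 14.25% | 12.75 | 0.45 |
| 15% / 5% | 27.75% | 14.6% | 13.1 | 0.45 |
| 5% / 15% | 29.25% | 13.9% | 15.4 | 0.39 |
| 10% / 20% | 28.5% | 13.5% | 15.0 | 0.39 |

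The first row runs from 11.6 points (s = 0.25) to 13.9 (s = 0.75). With equal true rates of 22.5%, non-response of 20% / 10% gives 20.25% against 21.4%, a spurious difference of 1.1 points. Swapping the arms reverses its sign.

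**5. Which imputation works.** Take 20% RBL / 10% HAL non-response and s = 0.5, with the same share of recurrences treated and recorded among responders.

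- *Imputing untreated non-responders at the overall observed arm rate.* RBL: (0.24 + 0.03)/(0.80 + 0.03) = 32.5%. HAL: (0.135 + 0.0075)/(0.90 + 0.0075) = 15.7%. The difference is 16.8 points, which overshoots.
- *Imputing from responders without recorded further treatment.* RBL: their recurrence rate is 0.15/0.85 = 17.6%. Untreated non-responders are 0.20 × 0.85 = 17% of the arm and add 0.17 × 0.176 = 3.0 points. The total is 24 + 3 + 3 = 30%. HAL: 0.075/0.925 = 8.1%, and 0.0925 × 0.081 adds 0.75 points. The total is 13.5 + 0.75 + 0.75 = 15%.

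The second approach recovers the true rates if response is unrelated to outcome given arm and treatment record.

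**The case against.** The strongest reply is that no rule for coding a silent non-responder is written. The sentence about drop-out sits in sample-size text, and missing-data handling commonly belongs in an analysis plan, which is not shown. That stands as far as it goes. A reader might infer that the protocol prescribes non-recurrence for these patients, but it does not. That coding follows from the exhaustive list of drop-outs and is not stated. The point therefore rests on what the article does assert: who counts as lost, and that the impact is minimal.

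A reader might also infer that records cannot show recurrence at all, or that outpatient re-banding would be missed. Neither is supported. Recorded further treatment puts a patient in the unfavourable category, and notes may mention persisting symptoms. Methods/design and Outcomes already seek any further treatment from hospital records, consultants and GPs, which would include banding. The narrower wording under Proposed sample size is a mismatch to reconcile.

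The 10% loss in the earlier study came from clinical follow-up only, whereas this trial adds a telephone interview and record searches. It is not a forecast of telephone non-response here. Nor do the documents say which arm would respond less, so quoting only the 20% RBL / 10% HAL case would overstate the harm: the reverse leaves the difference at 15.0 points.

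**Conclusion.** The concern holds as a matter of outcome definition and hidden missingness. It is not a sample-size error. Patients with traceable notes and no answer are counted as followed up, yet their rating is unobserved unless the records show recurrence. The under-5% loss and the minimal impact are therefore unsupported for the patient-reported component.

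With equal non-response at the document's own 5% or 10%, power at 175 per group stays at about 88% to 92%. With a 10-point imbalance between arms and half of recurrences visible in records, the bias is about 2 points downward when RBL responds less. When HAL responds less it is 0 to 0.4 points upward at the planned rates, and the odds ratio then moves from 0.41 to 0.39. If the true rates are equal, the bias is about 1 point in either direction. These sizes rest on assumed non-response and visibility, and on non-responders having the same true recurrence rate as responders.

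**What to change.** - Count recorded further treatment for haemorrhoids as recurrence for every patient, whether or not the 12-month question was answered.
- Treat no 12-month answer plus no recorded further treatment as missing. Multiply impute the rating from responders who also had no recorded further treatment, using arm, centre, baseline covariates and the six-week symptom score.
- Keep the records-only classification as a sensitivity analysis.
- Reconcile the record search under Proposed sample size (complications and operative procedures) with further treatment as used in Methods/design and Outcomes.
- Restate the under-5% figure as excluding missing patient ratings, and give the expected non-response to the 12-month question.

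The cost is a change of wording and a standard imputation, with a slightly wider interval and a higher stated missing rate. The imputation still assumes that response is unrelated to outcome given the variables used. The rule should be fixed before outcome data are seen, because it changes both numerator and denominator of the primary outcome.

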### Interventions

The intervention is either RBL or HAL. Both interventions are established and well documented procedures. Both intervention arms are considered standard care by NICE.

Conventional RBL uses a simple suction device that is applied to each haemorrhoid via a disposable proctoscope. A rubber band is then fired onto the base of the haemorrhoid which constricts the blood supply causing it to become ischaemic before being sloughed approximately 1–2 weeks later. The resultant fibrosis reduces any element of haemorrhoidal prolapse that may have been present. This is a very commonly performed procedure in all SOPCs; figures from an audit of current practice at STH over 20 such procedures are carried out every week. The procedure is a basic surgical skill that all senior staff are familiar with and competent in performing.

HAL uses a proctoscope modified to incorporate a Doppler transducer. This enables accurate detection of the haemorrhoidal arteries feeding the haemorrhoidal cushions. Accurate ligation of the vessels with a suture reduces haemorrhoidal engorgement. When combined with a ‘pexy’ suture, both bleeding and haemorrhoidal prolapse is addressed. All surgeons participating in the trial will ensure the need for a pexy suture is routinely assessed and recorded.

The procedure is simple, uses existing surgical skills and has a short learning curve, with the manufacturers recommending at least 5 mentored cases before independently practising. All surgeons involved in the study will have completed this training and will have carried out over 5 procedures prior to recruiting to the study.

